# STOP: an open label crossover trial to study ICS withdrawal in patients with a combination of obesity and low-inflammatory asthma and evaluate its effect on asthma control and quality of life

**DOI:** 10.1186/s12890-022-01843-0

**Published:** 2022-02-05

**Keywords:** Asthma, Obesity, T2-low, Corticosteroids, ICS tapering, RCT

## Abstract

**Background:**

Asthma patients with obesity often have a high disease burden, despite the use of high-dose inhaled corticosteroids (ICS). In contrast to asthmatics with normal weight, the efficacy of ICS in patients with obesity and asthma is often relatively low. Meanwhile, patients do suffer from side effects, such as weight gain, development of diabetes, cataract, or high blood pressure. The relatively poor response to ICS might be explained by the low prevalence of type 2 inflammatory patterns (T2-low) in patients with asthma and obesity. T2-low inflammation is characterized by low eosinophilic count, low Fractional exhaled NO (FeNO), no clinically allergy-driven asthma, and no need for maintenance oral corticosteroids (OCS). We aim to study whether ICS can be safely withdrawn in patients with T2-low asthma and obesity while maintaining an equal level of asthma control. Secondary outcomes focus on the prevalence of ‘false-negative’ T2-low phenotypes (i.e. T2-hidden) and the effect of ICS withdrawal on parameters of the metabolic syndrome. This study will lead to a better understanding of this poorly understood subgroup and might find new treatable traits.

**Methods:**

The STOP trial is an investigator-initiated, multicenter, non-inferiority, open-label, crossover study aiming to assess whether ICS can be safely withdrawn in adults aged 17–75 years with T2-low asthma and obesity (body mass index (BMI) ≥ 30 kg/m^2^). Patients will be randomly divided into two arms (both n = 60). One arm will start with fixed-dose ICS (control group) and one arm will taper and subsequently stop ICS (intervention group). Patients in the intervention group will remain ICS naïve for ten weeks. After a washout of 4 weeks, patients will crossover to the other study arm. The crossover study takes 36 weeks to complete. Patients will be asked to participate in the extension study, to investigate the long-term metabolic benefits of ICS withdrawal.

**Discussion:**

This study yields valuable data on ICS tapering in patients with T2-low asthma and obesity. It informs future guidelines and committees on corticosteroid-sparing algorithms in these patients.

*Trial registration* Netherlands Trial Register, NL8759, registered 2020–07-06, https://www.trialregister.nl/trial/8759.

**Protocol version and date:** version 2.1, 20 November 2020.

## Background

Asthma is a highly prevalent chronic pulmonary disease characterized by wheezing, shortness of breath, and cough. Asthma has a significant disease burden [1] and is considered an umbrella diagnosis for several phenotypes and endotypes. Endotypes may broadly be described as T2 high and T2 low asthma, dependent on the inflammatory mechanisms that drive the disease. Patients with asthma and obesity represent a phenotype frequently characterized by the absence of type 2 inflammation. In these patients, evidence for increased activation of central type 2 inflammatory cells is usually absent. The lack of type 2 inflammation (i.e. T2 low asthma) may explain the poor response to corticosteroids in patients with asthma and obesity [2–6], as central type 2 inflammatory cell types, such as T-helper 2 cells and eosinophils are major targets for corticosteroids and biologicals [7]. Nevertheless, almost all asthma patients are treated with inhaled corticosteroids (ICS), as recent guidelines advocate ICS as a cornerstone of asthma treatment without any distinction of the various asthma phenotypes [8]. As a result, patients with T2-low asthma and obesity are exposed to the side effects of corticosteroids without experiencing positive effects on their asthma symptoms. Side effects include adrenal insufficiency, cardiovascular disease, enhanced appetite, weight gain, hyperglycemia, osteoporosis, neurocognitive symptoms, and an increased risk of infectious disease [9–14].

These side effects can be prevented by minimizing ICS dosage. Dose reduction has been studied before, initially to induce asthma exacerbations and later to study dose optimization algorithms, but did not result in a successful ICS discontinuation strategy [15–22]. However, important clues were reported. For example, ICS tapering was better tolerated in patients with low blood or sputum eosinophils, suggesting lower ICS efficacy in patients with T2-low asthma [18–21]. A recent study by Heaney et al. used a dose guiding algorithm including blood eosinophils, Fractional exhaled NO (FeNO) and/or Periostin to adapt ICS dose [18–22]. This algorithm successfully reduced the cumulative dose of ICS when compared to usual care. However, complete ICS withdrawal was achieved in just 5% of all patients: these patients had a T2-low asthma [22]. Therefore, low success-rates of complete ICS withdrawal might be contributed to the high prevalence of T2-high asthma in prior studies. Therefore, to study ICS withdrawal, a clear distinction on T2 endotype should preselect patients with low ICS efficacy.

### Objectives

In this trial, we withdraw ICS in patients with T2-low asthma and obesity to determine the effects on asthma control. We hypothesize that ICS withdrawal is non-inferior to ICS continuation in patients with asthma and obesity. Additionally, this trial uses common T2-biomarkers to detect patients that become T2-high after ICS withdrawal; T2-hidden asthma.

## Methods

### Study design

The STOP trial is initiated by the ‘STZ center of Excellence for Asthma and COPD’ of the Franciscus Gasthuis & Vlietland hospital, collaborating with the Maasstad hospital and the Albert Schweitzer hospital. This multicenter approach ensures a larger number of possible study subjects and decreases selection bias due to social-economical differences between regions of Rotterdam. Patients will be randomized into one of two study groups to avoid allocation bias. Both groups consist of a control period and an intervention period in a 2 × 2 crossover pattern that creates balanced groups maximizes statistical power, and allows for analysing a possible sequence effect. The study has a non-inferiority design, which tests the hypothesis that ICS tapering is not inferior to ICS continuation. This intervention trial has an open-label to determine the effects of ICS tapering in a real-life situation.

### Population

Adults aged between 18 and 75 years with a Body Mass Index (BMI) ≥ 30 kg/m^2^ and a confirmed T2-low asthma diagnosis will be recruited at the outpatient clinic of the pulmonary departments of three major hospitals in the region of Zuid-Holland, the Netherlands; Franciscus Gasthuis & Vlietland hospital (Rotterdam), Maasstad hospital (Rotterdam), and Albert Schweitzer hospital (Dordrecht). In- and exclusion criteria must be met before the start of the run-in period. A detailed description of the in- and exclusion criteria can be found in Fig. 1.

**Fig. 1 Fig1:**
[figure not shown]
Overview of in- and exclusion criteria. 1) 12% reversibility in FEV1 or positive histamine/methacholine provocation test. 2) Allergic sensitization as proven by a skin prick test or specific IgE in combination with clinically relevant symptoms triggered by culprit allergen (Ansotegui, WAO position paper 2020). 3) 400–800 mcg beclomethasone daily (or dosisequivalent of other ICS). 4) Immune suppressive drugs, such as biologicals/monoclonal antibodies, calcineurine inhibitors, mTOR inhibitors and IMDH inhibitors. 5) in concordance with the Medical Research Involving Human Subjects Act (Dutch: WMO—article 5). (*BMI* Body Mass Index, *FeNO* Fractional exhaled Nitric Oxide, *OCS* Oral CorticoSteroids, *ICS* Inhaled CorticoSteroids, *FEV*_1_ Forced Exhaled Volume in 1 s, *ACQ* Asthma Control Questionaire, *COPD* Chronic Obstructive Pulmonary Disease)

### Randomization and blinding

Patients included in the study will be randomized into two groups: the first group with sequence Intervention-Control and the second group with sequence Control-Intervention. Randomization is performed by Castor Data Capturing software using variable block randomization with block sizes of 4/6/8 and stratification by study centre.

### Study procedures

All patients start with a run-in period of 4 weeks using a fixed dose of ICS (Fluticasone 1000mcg/day) as well as salbutamol 100mcg ‘as needed’ (see Fig. 2 and Table 1). This will equalize baseline ICS-exposition. (The period of 4 weeks is similar to earlier tapering studies [15–21]).

**Fig. 2 Fig2:**
[figure not shown]
**A** Schematic overview of the STOP trial: a 4 week run-in, followed by either an intervention period or a control period of 14 weeks, followed by a crossover. After completion of both treatment periods, patients may choose to participate in the extension study. **B** All patients will be enrolled with a prescription of Fluticasone 1000 mcg and Salbutamol 100 ug (as needed). **C** Patients receive a stable dose of ICS during the control period. **D** During the intervention period, patients half the dose of Fluticasone every 2 weeks. Patients will discontinue ICS after 4 weeks and remain ICS naïve for 10 weeks

**Table 1 Tab1:** Overview of procedures during STOP trial. These procedures will be used in both crossover period 1 and crossover period 2

	Time (weeks)	− 2	0 and 18	4 and 22	6,8,13 and 24,26,31	18 and 36
	Period (1 or 2)	1	1 and 2	1 and 2	1 and 2	1 and 2
	Visit type	Inclusion	Run-in	Baseline	Follow up	Follow up
Activity/Assesment						
Live		x	x	x		x
Telephone					x	
Check inclusion criteria		x				
Informed consent		x				
Medication check		x				
Prior medical history		x				
Comorbidities		x				
Anthropometrics		x		x		x
Exacerbation frequency		x	x	x	x	x
Questionnaires		x	x	x	x	x
Blood samples				x		x
Scalp Hair				x		x
Lung function test*			x	x		x
eNose				x		x
Study information		x	x	x	x	x
Prescriptions			x	x	x	x
SAE form		Thoughout study				

After the run-in period, patients in arm 1 will discontinue ICS (intervention), while patients in arm 2 will continue with a fixed-dose ICS for 14 weeks (control). An abrupt stop of ICS might cause asthma flair-ups. Therefore, ICS-dose will be tapered in two steps (fluticasone 500mcg/daily and 250 mcg/daily) over 4 weeks (see Fig. 1). After those 4 weeks, patients will become ICS-naïve for 10 weeks. Similar studies (which typically had a mix of both T2-high and T2-low patients) used an ICS naïve duration between 20 days and 10 weeks, of which 8 weeks and 10 weeks were most commonly used [15–21]. Empty canisters of salbutamol or fluticasone will be collected and weighed to evaluate protocol adherence.

After completing the first period, patients will crossover from the intervention arm to the control arm and vice versa. There is a-4 week washout/run-in period between the first and second periods to avoid carry-over effects. A second baseline ensures analysis of sequence effects. After completion of the second intervention period, intervention- and control data will be compared. The trial results will be shared with the participants and other relevant parties during a ‘patient participation meeting’.

This design is powered on demonstrating sustained asthma control, with a limitation in terms of measuring long-term health benefits (e.g. metabolic alterations) of ICS tapering. To study the long-term effects of ICS withdrawal in T2-low asthma patients with obesity, we will extend the study by 2 years in an open-label extension study. In this extension study, patients will remain ICS naïve. Patients may only participate in the extension study after successful discontinuation of ICS in the crossover period.

### Outcomes

#### Primary endpoint

The primary parameter is the ACQ-5, which is widely used in the Netherlands to monitor asthma control. The difference between the control and intervention periods will be analysed using the baseline ACQ-5 score as a reference [23].

#### Secondary study parameters

**Anamnestic parameters**
Exacerbation frequency (mild/intermediate/severe)MedicationSmoking status and exposure to drugs/vapors/fumes/gases/other chemicalsSocial-economic statusAge at asthma diagnosisCo-morbidity (such as hypertension, OSAS, cardiovascular disease, stroke, diabetes, kidney failure, gastrointestinal reflux, malignancy, osteoporosis)Birth weight and respiratory history during childhoodAdverse eventsAdherence to treatment regimen (using the weight of the inhaler at study visits)

**Questionnaires**
**ACQ-5:** In this study the ACQ-5 will be used, consisting of five patient self-reported questions. The recall time is one week with a score range of 0 to 6 (0 = never and 6 = always). A higher score is associated with worse asthma control. The minimal clinically important difference of the ACQ is 0.5 [23].**AQLQ:** The AQLQ consists of 32 items with a 3 week recall period. The score range per question is 1 to 7 (1 = severely impaired and 7 = not impaired at all). It is used to qualify the disease-specific health-related quality of life [24–26].**MRC:** The MRC (Medical Research Council) is a dyspnea scale, as a measure of disability in patients with respiratory disabilities. It consists of one question about the shortness of breath and six possible answers. The score range per question is 0 to 5 (0 = no shortness of breath at all and 5 = too breathless to leave the house). A higher score is therefore associated with a high burden of disease [27].**FSS:** The FSS (Fatigue Severity Scale) measures fatigue severity. It has 9 items with are scored on a 7 point Likert scale. A higher score is associated with higher fatigue severity [28].

**Anthropometrics**
Body Mass Index (BMI)Waist circumferenceBlood pressure

**Blood tests**
**Metabolic and endocrine panel:** Oral corticosteroids are none for their dysregulating effects on glucose homeostasis [29]. This dysregulation was not seen in retrospective studies [30]. However, prospective studies comparing asthma patients with and without ICS have not been performed recently, as guidelines recommend ICS in all patients [31–33]. The design of this study fits the requirements for such an analysis. The following parameters will be tested at baseline, intervention period and control period: fasting glucose/insulin, morning cortisol, lipid spectrum, and liver function tests.**Pulmonary panel:** Inhaled corticosteroids suppress T2-high inflammatory pathways. Previous ICS tapering studies (mainly including patients with T2-high asthma) demonstrated increased blood eosinophils after ICS tapering or even used an ICS dosing algorithm based on blood eosinophils [15, 22]. However, these studies had no differentiation between T2-high and T2-low asthma. This trial solely includes patients with T2-low asthma during treatment with ICS and suspect these pulmonary parameters to remain low after ICS withdrawal. However, we postulate the presence of T2-hidden phenotypes, in which pulmonary biomarkers increase after ICS tapering. To study this phenomenon, a pulmonary panel will be tested, including blood eosinophils, total IgE and hematologic parameters.**Blood Serum:** Blood serum will be isolated and frozen at − 80 °C for analyses of inflammatory and endocrine biomarkers.**Isolation of Peripheral Blood Mononuclear Cells (PBMCs)**: To study the effect of ICS withdrawal on T2-low inflammatory cells.

**Lung function**
**Expiratory flow assessment:** A hand-held spirometer will be used to assure maintained lung function after ICS withdrawal by measuring the FEV1.**FeNO:** Patients in this study have a starting FeNO lower than 20 ppb. However, we postulate that the FeNO values may increase to a value larger than 20 after ICS withdrawal. These patients have become T2-high (e.g. T2-hidden), which is an important secondary outcome.**eNose:** The electronic Nose is a novel development that uses semiconductors to measure patterns of exhaled volatile compounds. A eNose test results in a so-called ‘breath print’. The eNose successfully predicted response to (lung-)cancer treatment and is also used to measures the effect of corticosteroids in patients with Asthma [34–37]. We aim to study the relationship between breath print and treatment response to predict successful ICS withdrawal. Furthermore, the eNose might be able to predict the response to ICS in ICS naïve patients with newly diagnosed asthma.

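### The same 20 ppb FeNO cut-off selects patients and later labels them T2-hidden, so the raw share above 20 ppb after withdrawal overstates how much type 2 inflammation ICS was masking

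*Protocol article*

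**What the plan says.** The FeNO entry under Secondary study parameters, Lung function, makes three statements in sequence:

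- Selection: "Patients in this study have a starting FeNO lower than 20 ppb".
- Expected event: "we postulate that the FeNO values may increase to a value larger than 20 after ICS withdrawal".
- Label: "These patients have become T2-high (e.g. T2-hidden), which is an important secondary outcome".

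The Abstract (Background) names the quantity of interest: "Secondary outcomes focus on the prevalence of ‘false-negative’ T2-low phenotypes (i.e. T2-hidden". The Objectives section adds that T2 biomarkers will be used to detect patients who turn T2-high once ICS is withdrawn.

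On timing, the Population section states: "In- and exclusion criteria must be met before the start of the run-in period". The selecting value is therefore obtained before run-in.

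Three other places bear on the point:

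- Under Blood tests, T2-hidden is also linked to other markers: "a pulmonary panel will be tested, including blood eosinophils, total IgE and hematologic parameters". No rule for combining them with FeNO is given.
- Table 1 has a row "Lung function test", marked at the run-in visit, the baseline and the last visit of both periods (the last visits are weeks 18 and 36). FeNO is listed under the lung function heading.
- The Statistical analysis section plans to compare secondary variables between intervention and control, and to use generalised estimating equations (GEE) with a logit link for categorical ones.

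**The concern.** Entry and event share one cut-off. The printed rule asks for no minimum rise, no confirming reading and no comparison with the same patient on continued ICS. Once everyone reading above 20 ppb has been excluded, chance movement relative to the cut-off can only be upward. Some patients will later read above 20 ppb whether or not ICS was suppressing anything, and the text would count them as having become T2-high through withdrawal.

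At stake is the prevalence of T2-hidden asthma, which the abstract puts forward as a secondary focus. A raw proportion mixes three groups: patients unmasked by withdrawal, patients whose true FeNO was above 20 ppb all along but who read low at entry, and patients whose true FeNO is at or below 20 ppb and who read high once. Only the first group answers the question in the Objectives.

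**Working it through.** **The document's only computed figure.** This is the sample size, and it reproduces. The variance of the within-patient difference is 2 × 0.7847 × (1 − 0.5) = 0.7847. Then n = 0.7847 × (1.645 + 1.282)² / 0.25² = 108 after rounding up, and 108 / 0.90 = 120. The point below does not touch it; 108 is used only to turn rates into patient counts.

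**Inputs from the document.** Entry FeNO below 20 ppb; label at FeNO above 20 ppb after withdrawal; FeNO obtainable at the end of both periods.

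**Inputs not in the document (assumptions).** True FeNO is log-normal across the screened population, with median m and between-patient log-SD b. Each reading adds independent within-patient error with log-SD w. Entry rests on one reading. Withdrawal has no effect.

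**Step 1: one patient with a fixed true value T.** For a within-patient coefficient of variation CV, w = √ln(1 + CV²), and

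P(later reading > 20) = 1 − Φ[(ln 20 − ln T) / w].

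For T = 18 and CV 20%: w = √ln 1.04 = 0.198; (ln 20 − ln 18) / w = 0.105 / 0.198 = 0.53; P = 29.7%. Over CV 10% to 30% this runs from 14.5% to 36.0%. For T = 14 it runs from 0.0% to 11.2%. The effect comes from patients near the cut-off.

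**Step 2: the selected population.** Simulation of P(later > 20 | entry < 20), with 2,000,000 patients per setting and no effect of withdrawal. Over m = 12-18, b = 0.35-0.5 and w = 0.15-0.35, the crossing rate is about 4% to 28%. The middle cases (w = 0.25) are:

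| m (ppb) | b | Crossing rate | Of 108 | Share of crossers with true FeNO > 20 | Crossers with true FeNO ≤ 20, as % of all selected |
|---|---|---|---|---|---|
| 14 | 0.50 | 11.3% | 12 | 38% | 6.9% |
| 14 | 0.35 | 11.8% | 13 | 29% | 8.4% |
| 16 | 0.50 | 14.4% | 16 | 43% | 8.2% |
| 16 | 0.35 | 16.7% | 18 | 36% | 10.6% |

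A second parameterisation (geometric mean 14-20 ppb, between-patient geometric SD 1.5, CV 10-30%) gives 4.6% to 27.2%. Its mid case (geometric mean 16, CV 20%) is 12.8%, about 14 of 108.

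**Step 3: candidate repairs under the same null.** A sound estimate of masking should return zero.

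| Rule | Result with no effect |
|---|---|
| Above 20 ppb off ICS (as printed) | about 4-28% |
| Above 20 ppb off ICS and not above 20 ppb at end of control | about 2.5-15% |
| Proportion above 20 ppb off ICS minus proportion at end of control | about 0% in every setting |

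The second rule stays inflated because a patient near the cut-off can read high at one visit and low at another by chance. The paired difference cancels because such crossings are equally likely in both directions.

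**The case against.** The FeNO text sits in a list of measurements and is phrased as a postulate. It names no visit and does not rule out a confirming reading. Such operational detail often belongs to a full protocol or analysis plan, and neither is shown. That would answer a complaint about a missing definition. Here a definition is printed, and followed as written it is biased in a known direction. This part of the objection tempers the point but does not remove it.

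A reader might infer more than the document supports, in three ways:

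- **That FeNO alone decides T2-hidden status.** The blood-test section also ties it to eosinophils and other markers. An any-marker rule would add chance crossings and a joint rule would reduce them, so the effect on a final composite prevalence is unknown.
- **That no control comparison is foreseen.** The analysis section plans intervention-versus-control comparison and a logit GEE for categorical variables. What is absent is any link between those methods and the T2-hidden label or its prevalence.
- **That 12-18 of 108 patients will be falsely labelled.** That count rests on assumed FeNO variability. In addition, 29-43% of those crossers truly exceed 20 ppb. They were not unmasked by withdrawal, but they were wrongly taken as T2-low, which is close to the abstract's own idea of a false-negative phenotype. Crossers with true FeNO at or below 20 ppb are about 7-11% of the selected patients.

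**Conclusion.** The point stands in a limited form. As printed, the raw share above 20 ppb after withdrawal overstates the prevalence of ICS-masked asthma. The direction follows from selection at the same cut-off together with any within-patient variation, and needs no outside figure.

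The size does need outside figures, because the document gives neither the distribution nor the repeatability of FeNO. The range of about 4-28% holds only under the stated assumptions of log-normal FeNO, independent errors, a single entry reading and no effect of withdrawal. It measures crossing not caused by withdrawal, part of which is misclassification at entry rather than noise around a truly low value.

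The consequence is confined to the FeNO-based part of a secondary outcome. The ACQ-5 comparison and the 120 patients are unaffected. The change should be made, but it does not put the trial's main conclusion at risk.

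**What to change.** In the analysis section, state that the proportion of patients with FeNO above 20 ppb will be reported at the end of the withdrawal period and at the end of the control period. The within-patient difference (withdrawal minus control), with a confidence interval, is then the estimate of T2-hidden prevalence attributable to withdrawal. The planned logit GEE with treatment and period can supply it. Since that model yields an odds ratio, the difference should be taken from its fitted probabilities.

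If a patient-level label is wanted (above 20 ppb off ICS and not above 20 ppb at end of control), present it as descriptive only, because it still labels roughly 2.5-15% under no effect. State also how FeNO combines with the blood markers.

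Cost: a few sentences, with no new visit, test or patient, since Table 1 already schedules lung function tests at the end of both periods. The reported prevalence will probably be lower and its interval somewhat wider. In the 12.8% mid case with 108 patients, the 95% half-width of the raw proportion is 1.96 × √(0.128 × 0.872 / 108) = 6.3 percentage points. With 7.1% of patients discordant in each direction, that of the paired difference is 1.96 × √((0.071 + 0.071) / 108) = 7.1 points.
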